# Engaging primary care professionals in collaborative processes for optimising type 2 diabetes prevention practice: the PREDIAPS cluster randomised type II hybrid implementation trial

**DOI:** 10.1186/s13012-018-0783-0

**Published:** 2018-07-11

**Keywords:** Pre-diabetes, Primary health care, Prevention, Cluster clinical trial, Implementation strategy, Interprofessional collaborative practice

## Abstract

**Background:**

There is a lack of evidence concerning the effectiveness of different strategies to engage healthcare professionals in collaborative processes that seek to optimise clinical practice. The PREDIAPS project aims to assess the effect of different primary health care (PHC) providers’ engagement procedures in the creation and execution of a facilitated interprofessional collaborative process to optimise the integration of the recommended clinical practice for the prevention of type-2 diabetes (T2D) in routine PHC.

**Methods:**

This will be a randomised cluster type II hybrid implementation trial. Nine PHC centres from the Basque Health Service (Osakidetza) will be allocated to two different procedures to engage family doctors and nurses and create an interprofessional collaborative practice to optimise the integration of a T2D primary prevention programme. All centres and PHC professionals will receive training on current guidelines in primary prevention of T2D and effective interventions to promote healthy lifestyles. Headed by a local leader and an external facilitator, centres will conduct a collaborative structured process to model and adapt the intervention and its implementation to the specific context of professionals and centres. One of the groups will apply this strategy globally, promoting the cooperation of all health professionals from the beginning. The other will perform it sequentially, centred first on nurses, who will then seek the pragmatic cooperation of doctors. All patients without diabetes aged ≥ 30 years old who attend collaborating centres at least once during the study period and found to be at high risk of developing T2D will be eligible for programme inclusion. The main outcome measures focus on changes observed in indicators of T2D prevention clinical practice at centre level after 12 and 24 months, associated with the application of one or other engagement procedure. Secondary outcomes will compare their clinical effectiveness in changing eligible exposed patients’ main lifestyle behaviours and risk factors (physical activity and diet, weight, etc.) after 12 months.

**Discussion:**

The PREDIAPS project will generate scientific knowledge on procedures for engaging PHC professional to facilitate feasible and effective adoption of proven interventions for the prevention of T2D in routine clinical practice through the application of implementation strategies.

**Trial registration:**

Clinicaltrials.gov identifier: NCT03254979. Registered 16 August 2017.

## Background

The dramatic increase in the rates of type 2 diabetes mellitus (T2D) and associated complications has made it a major health problem worldwide [1]. Despite the growing evidence provided by landmark T2D prevention trials and several translational studies assessing both the efficacy and effectiveness of healthy lifestyle prevention interventions in clinical and community settings [2–12], the actual translation and integration of primary prevention programmes in routine clinical practice remains an unsolved challenge. Indeed, currently, in the real context of the provision of services seeking to prevent T2D in the Basque Health Service (Osakidetza), only 30% of patients at high risk of developing this disease receive some type of intervention focused on preventive advice.

In the PreDe multicentre trial conducted in 14 Osakidetza PHC centres, it was shown that an intervention promoting healthy lifestyles among patients at high risk of developing the disease succeeded in reducing the incidence of T2D by almost a third (32%) [12]. Nevertheless, despite having identified an intervention that is potentially effective for preventing T2D in PHC, the passive implementation strategy used for guiding the translation and adoption of the intervention in a routine clinical context by our health professionals has not achieved feasible and sustainable deployment, with low levels of adoption by clinicians, limited population coverage, failure to integrate the intervention into practice, and lack of continuity at the end of the project, among other problems. The factors identified by the professionals as the main barriers that constrained the feasibility of integration of the programme under routine conditions in the centres and implied that it would not be sustainable were the lack of participation and commitment from the staff of the centres in the context of time pressures and heavy workloads. These two factors, in turn, limited the organisation of operational elements required for putting the programme and its components into practice, in an environment with few incentives and an overload of corporate initiatives [13].

Numerous strategies for changing clinical practice have been tested with variable degrees of success. There is a consensus in the scientific literature that passive learning or dissemination strategies are ineffective [14]. In contrast, key elements in the success of implementation strategies seeking to optimise clinical practice include internal leadership to drive change and implementation [15, 16], active and participatory engagement of professionals in collaborative processes [17–19], external facilitation [20, 21], adaptation of interventions to the local context and its determinants [22, 23], and the combination of multiple components [14]. Among these effective elements, one of the areas for which there is still a lack of clear evidence concerns the effectiveness of strategies for engaging professionals in the aforementioned collaborative innovation processes [19, 24–26]. It is not known what factors are essential for effective interprofessional collaboration, especially in the real-world of PHC, with the overall context of overcrowding and work overload, and marked differences by professional category, both in terms of identity and competencies [19].

Interprofessional collaboration (communities of practice, work teams or collaborative interprofessional processes) has long been considered an essential factor underpinning effective PHC [27]. In general, the practice of interprofessional collaboration characterised by mutual respect and trust, open communication between individuals, holding a shared vision of the goals and potential benefits of the intervention, as well as joint decision-making by consensus on how the intervention should be implemented, has been shown to improve clinical practice and health outcomes [15, 19, 20, 28–30]. Yet, the mere placing of healthcare professionals with different backgrounds in a team does not mean that they will have the knowledge or skills necessary to work together and collaborate. Further, there is evidence that the effective implementation of change in organisations is often obstructed by organisational and professional demarcations that hinder the sharing of knowledge and dissemination of working practices [25, 31-33]: professional differences may have a dual effect leading, on the one hand, to innovation, learning and cross-fertilisation between practices, but on the other, to division, fragmentation and disconnection. Great efforts are needed to overcome such professional boundaries and create functional interprofessional collaboration, given its complexity [19].

Research on interprofessional work teams and collaborative communities of practice establishes that collaboration is an interpersonal process that requires joint engagement in intellectual activities and that interaction between members of the team, concerning the assignment of functions and limits between professionals, hinge on two principal concepts: independence and collaboration [34–36]. Collaboration is an interpersonal process implying joint participation in intellectual activities, while independence is associated with independent self-determined practice [36]. These concepts of collaboration and independence have emerged as complementary factors that may improve the provision of health services, though in extreme cases, they may disrupt the work of a team. Based on theoretical models of the engagement of health professionals and research in the field, a spectrum of strategies for engagement in cooperative practices that favour interaction between different types of professionals have been identified, ranging from not promoting any type of relationship or engagement—“Individualism”, through encouraging some degree of closeness between groups—“Creation of relations”, to affirming a common identity that includes all the groups—“Promotion of a common identity” [26]. Hence, on the basis of the few studies conducted in this field, it seems that independence may be an important element in the functioning of an interprofessional team. The empowerment of members of the team to develop their independence may improve collaborative interactions. While an ability to swap roles and functions may help to reduce the work load of group members, it may also increase the level of conflict related to fighting for power as the roles of the different professionals are less well defined [35].

Specific objectives are the following:To estimate the effectiveness attributable to the strategy for engaging health professionals in the improvement of the clinical practice for preventing T2D in high risk individuals, comparing the following implementation indicators between the centres assigned to the sequentially facilitated collaborative model strategy and those assigned to the globally facilitated collaborative model strategy.To estimate the potential clinical effectiveness of the intervention programmes comparing the proportion of users who change their lifestyle habits (physical activity and diet) and lose 5% of their body weight (a) observed in the population exposed (pre-post comparison) in both groups and (b) comparing the figures obtained in the programmes following the sequential vs the global strategy.To analyse the factors associated with successful implementation results in the implementation strategy in general and in the engagement procedures assessed in particular, at the organisational collaborating health professional and exposed patients levels.To explore the perceived feasibility and satisfaction of health professionals and users exposed with the implementation processes and the intervention programmes.

## Methods

### Design

This is to be a multicentre randomised type II hybrid implementation trial of feasibility and potential effectiveness in nine primary care centres that will be randomly allocated to one of the two strategies for engaging healthcare professionals in the development and execution of a process for adopting the recommended clinical practice for T2D prevention: a global strategy, seeking cooperation between professionals at all levels from the outset; or a sequential strategy, first led by nurses, and then seeking the pragmatic cooperation of the rest of the professionals in the centres. The research protocol has been approved by the Basque Country Clinical Research Ethics Committee (Ref. no.: 08/2015).

### Participants

#### Primary care centres

Nine PHC centres of Osakidetza will be included in the study based on their organisational willingness to optimise the primary prevention of T2D, assessed through the obtaining of written commitment and consent to collaborate from a majority (> 51%) of the centre’s nurses and a substantial proportion of the doctors whose patients’ lists are involved through the nursing staff, after a session presenting the project.

#### Users of primary care services

All the patients aged between 45 and 70 years old who seek medical attention in the participating centres at least once with a high risk of developing T2D and/or with moderate hyperglycaemia (high baseline glucose levels or glucose intolerance), but no diagnosis of T2D documented the medical record, will be candidates to participate in the T2D prevention programme.

### Recommended clinical intervention based on evidence and clinical practice guidelines

Based on the available scientific evidence and clinical practice guidelines [2, 4, 13], three measures are recommended for the prevention of T2D in clinical settings:

(1) Screen for individuals with abnormal regulation of glucose or a high risk of developing T2D (fasting glucose ≥ 110–125 mg/dl, HbA1c ≥ 6%), with the following approaches being recommended: T2D screening as part of opportunistic screening for cardiovascular risk in individuals ≥ 45 years old or ≥ 30 years old with at least one known risk factor (e.g. hypertension); T2D screening based on a body mass index (BMI) ≥ 25 kg/m^2^ in individuals between 40 and 70 years old; or screening for T2D risk using the FINDRISC [13] scale in individuals between 45 and 70 years old. These last two procedures should be completed with a fasting glucose to discard T2D diagnosis.

(2) In patients identified as high risk, carry out a structured intensive programme focused on the prescription of personalised plans for lifestyle change (low-calorie and low-fat diets, and at least 150 min of exercise per week). This intensive intervention requires the assessment of lifestyle habits, personalised advice (tailored to the individual’s risk) and the setting of objectives and plans or prescription of a personalised intervention for lifestyle change. It should combine education with the use of theoretically-grounded evidence-based strategies for behavioural change and the introduction of changes in daily life.

(3) Ensure that the intervention is followed up to keep participants motivated, with frequent contact at the beginning and subsequently annual follow-up.

### Random allocation

The implementation strategy to facilitate the adoption of the recommended clinical intervention for T2D prevention will be common to the two comparison groups (see the following section). In order to distinguish and isolate any effects of the strategy used for the creation of the multidisciplinary community of practice, the centres will be randomly allocated to one of the comparison groups: five centres to the sequential strategy and the other four to the global strategy. This random allocation will be carried out by the members of our research unit not involved in this project, using a computer-generated random number sequence obtained before starting the trial. Given that the new programme is an optimisation of T2D prevention activities already offered by the Basque Health Service, it is expected that participating patients will be blinded to group allocation.

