In order to analyse the potential associated or modifying characteristics of the effect that the implementation strategy and, within it, the procedures for creating the community of practice could have on clinical practice in the primary prevention of T2D and on clinical outcomes, we studied various different factors at centre, health professional and patient levels:Health centre-based factors: Organisational willingness to change measured with the *Organizational Readiness for Knowledge Translation* (OR4KT) questionnaire [44], the Spanish version of the OR4KT instrument comprising 59 items assessing 6 dimensions and 23 sub-dimensions related to organisational predisposition to knowledge translation: organisational climate, organisational support, contextual factors, change content, leadership, and motivation; leadership assessed with the *Implementation Leadership Scale* (ILS) questionnaire [45]; and various characteristics of the primary care centres, namely, number of registered patients, number of healthcare professionals, mean number of registered patients per family doctor, and a socioeconomic deprivation index for the catchment area that combines variables related to employment (unemployment rate, manual and short-term employment) and education (educational attainment rate among young people and overall).Healthcare professional-related factors: sociodemographic variables (age, sex, professional group, etc.); and professionals’ healthy lifestyle behaviours; and Attitudes, knowledge and skills in the promotion of healthy habits in the clinical context, measured through the *Preventative Activity Questionnaire* [46].Patient-level factors: sociodemographic variables (age, sex, socioeconomic level- deprivation index, etc.); active health problems-morbidity (Adjusted Clinical Groups-ACG, etc.); and frequency of attendance.

Health professionals will be surveyed to obtain information related to the variables at health centre and professional level before the execution of the strategy, immediately after it and 12 months after the introduction of the programmes in the centres.4.Fidelity of the implementation strategy

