#### Management and quality of the data

All the data related to patient recruitment, the execution of the programme and the demographic characteristics of the users (age, sex, socioeconomic level) as well as the clinical variables (chronic health problems, biological and clinical parameters) will be obtained from the information extracted from the electronic health records of the Basque Health System. The Primary Care Research Unit of Bizkaia is explicitly authorised by the Healthcare Management of the Basque Health System to extract and use data from the electronic health records for research purposes. The coordination, process quality control and execution of the study, as well as management of data and ensuring its quality, are the responsibility of the Primary Care Research Unit of Bizkaia. The telephone interviews of the participants for the evaluation process of lifestyle changes will be carried out by trained professional interviewers, under the supervision of the research team. All the study data were treated anonymously and have been exclusively used for the objectives of the study. The confidentiality of personal data of participants was safeguarded at all times, in accordance with the organic law for personal data protection (15/1999 of December 13). Safety outcomes were not assessed because we did not anticipate any adverse effects due to the intervention given that it only involved physical activity and healthy diet promotion.

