#### Sample size

As a worst case scenario regarding the main outcome variables for the optimisation of practices for the prevention of T2D, we hypothesise that we will obtain a rate 30% higher than a baseline level of 50% (that is, 65% in the sequential group vs 50% in the global group) in several of the outcome variables. Considering the participation of 9 centres, an alpha level of 0.05, and an intra-class correlation coefficient (ICC) at centre level of 0.03, we will need a minimum of 425 patients at high risk of developing T2D to be exposed to the prescription of a personalised plan for lifestyle change per group (850 in total) to achieve a statistical power of 80%, allowing for a possible loss of 20% of patients, in the comparison of the aforementioned process indicators related to exposure and execution of the intervention. This scenario is reasonably plausible assuming that 50% of the doctors lists in the centres agree to collaborate with this research and if we consider that, according to data from OSABIDE, an average attendance per year of 875 patients over 45 years of age with prediabetes (baseline glucose ≥110 mg/dl) per group (175 per centre). For exploring a possible modification of clinical outcomes from the prescription of lifestyle changes, namely, a 5% loss of body weight, attributable to the creation of the community of practice, we need 616 patients (308 per group) to achieve a power of 80% to reject the null hypothesis H_0_:p1 = p2 using a bilateral chi-squared test for two independent samples with a level of significance of 5%, considering that 10% of patients will attain such change in one of the groups and 35% in the other, assuming an ICC of 0.03 and a possible loss of 10% of patients at 12 months.

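### Nine centres are split 5:4 at random with no balancing described, although centre factors that could be balanced are planned measures obtainable before allocation

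*Protocol article*

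**What the plan says.** Under Random allocation, the split is fixed as "five centres to the sequential strategy and the other four to the global strategy". It is drawn by research-unit members outside the project, "using a computer-generated random number sequence obtained before starting the trial". Neither that section nor any other mentions stratification, matching, minimisation or constrained randomisation.

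The article also plans to record several centre characteristics. Under Assessment of results, the health-centre factors include "number of registered patients, number of healthcare professionals, mean number of registered patients per family doctor, and a socioeconomic deprivation index". Table 2 takes the execution indicators, including prescription of a lifestyle plan, at baseline from the electronic health record. Under Management and quality of the data, the research unit is "explicitly authorised by the Healthcare Management of the Basque Health System to extract and use data from the electronic health records". The Sample size section already cites record-system counts of attenders with prediabetes.

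Under Analysis, the article plans pre-post differences within centres and between groups, with adjustment for confounders selected by forward and backward steps. The Discussion names the small number of centres only as a limit on generalisability.

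**The concern.** With nine units, randomisation alone gives no assurance that the arms start alike. The quantity compared between arms is in effect a mean over five centres against a mean over four. One or two unusual centres can therefore move it by an amount that matters next to the target effect.

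Adjustment after the event is limited. Nine centres in two arms leave 9 − 2 = 7 degrees of freedom between centres, enough to adjust for perhaps one or two centre-level factors, and the planned covariate selection is data-driven. The article also says it will judge results by the size of the differences, not by significance. Chance imbalance between centres enters that size directly. Once the centres have been allocated, balance cannot be restored.

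**Working it through.** The plan states no figure for baseline balance, so there is none to reproduce. The inputs come from its Sample size section: "Considering the participation of 9 centres, an alpha level of 0.05, and an intra-class correlation coefficient (ICC) at centre level of 0.03", and a target of "65% in the sequential group vs 50% in the global group", a difference of 15 points.

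**1. Spread between centres.** Assume that the ICC of 0.03 applies to a baseline rate of 50%.
- Between-centre SD = √(ICC × p × (1 − p)) = √(0.03 × 0.25) = 0.0866, or 8.7 points.

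**2. Chance difference between arms**, with centres weighted equally.
- SD = 0.0866 × √(1/5 + 1/4) = 0.0866 × 0.671 = 0.058, or 5.8 points.
- Taking centre rates as roughly normal:

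| Gap exceeds | Probability |
|---|---|
| 5 points | 0.39 |
| 7.5 points (half the target effect) | 0.20 |
| 10 points | 0.085 |

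**3. Sensitivity to the inputs.**

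| Baseline rate | ICC | SD of difference (points) | P(>5) | P(>7.5) |
|---|---|---|---|---|
| 50% | 0.01 | 3.4 | 0.14 | 0.03 |
| 50% | 0.03 | 5.8 | 0.39 | 0.20 |
| 50% | 0.05 | 7.5 | 0.51 | 0.32 |
| 50% | 0.10 | 10.6 | 0.64 | 0.48 |
| 30% | 0.03 | 5.3 | 0.35 | 0.16 |

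The 30% row uses the current service-wide figure for preventive advice given in the Background.

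**4. Several factors at once.** For one factor, a difference above one between-centre SD has probability 2 × (1 − Φ(1/0.671)) = 0.136. For at least one of three independent factors it is 1 − 0.864³ = 0.36.

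**5. What restriction would gain.** There are 9!/(5! × 4!) = 126 possible 5:4 splits. All were enumerated over repeated simulated sets of nine centres with three independent normal factors. Splits were ranked on the sum of squared standardised arm differences, and one was drawn at random from those kept.

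| Splits kept | P(>5) | P(>7.5) | P(>10) |
|---|---|---|---|
| 126 (all) | 0.39 | 0.20 | 0.08 |
| 63 (best half) | 0.20 to 0.22 | 0.05 to 0.06 | 0.01 |
| 32 (best quarter) | 0.10 | 0.01 | below 0.001 |

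**6. What restriction costs in a permutation test.** Attainable one-tail fractions at or below 0.05:
- All 126 splits: the six most extreme qualify, 6/126 = 0.048.
- 63 splits: the three most extreme qualify, 3/63 = 0.048.
- 32 splits: only the single most extreme qualifies, 1/32 = 0.031; the next is 2/32 = 0.0625.

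Keeping half therefore retains most of the gain without leaving a single qualifying split.

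**The case against.** The strongest reply is that simple randomisation of clusters is valid. Chance imbalance is imprecision, not bias, and the 5.8 points is the between-centre part of the standard error that the ICC and the multilevel model are meant to carry. This stands, and it is why the point concerns efficiency and face validity, not an invalid design.

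A second reply is that the planned analysis uses pre-post differences, so a raw baseline gap does not pass straight into the result. This also largely stands. If the centre-level correlation between baseline and follow-up is 0.7 to 0.9 (an assumption) with equal SDs, a 5-point baseline gap shifts the difference in change by (1 − 0.9) × 5 = 0.5 to (1 − 0.7) × 5 = 1.5 points, and by about nothing after baseline adjustment. The reply does not reach size, deprivation or other centre factors that act on the change itself. Nor does it reach adoption, the first main outcome listed: adoption of a new programme has no prior value, and Table 2 as shown gives no baseline for it.

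Third, a reader might infer that the trial used wholly unrestricted allocation with the centre data already in hand. The article does not support that. The 5:4 count is itself fixed, a condensed article may omit detail, and it nowhere says that centre values were held at randomisation. It shows only that they are planned measures and obtainable. Nor does it rank baseline rate, size or deprivation as the strongest predictors of the outcomes; the Background stresses staff participation, commitment and workload.

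Fourth, the screening indicator depends on a strategy that each centre chooses during the collaborative process, after allocation. A baseline screening rate is therefore an awkward balancing factor. The prescription rate does not have this problem.

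**Conclusion.** The point holds as an advisable improvement. The article describes no balancing of nine centres beyond the 5:4 count. At its own ICC there is about a 1 in 5 chance of a baseline gap above half the target effect.

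The size rests on four assumptions: the ICC of 0.03 applies to the baseline rate, centres weigh equally, centre rates are roughly normal, and (for the restricted figures) the factors are independent. Across ICCs of 0.01 to 0.10, P(>5 points) runs from 0.14 to 0.64.

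A reader might go further and conclude that the treatment comparison is biased, or that the raw gap should be set directly against the 15-point effect. Neither follows: the randomisation is sound, and the pre-post analysis absorbs much of a gap in the baseline rate. What remains exposed is adoption and the centre factors that nine clusters give little room to adjust for.

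**What to change.** Once all nine centres have joined, and before allocation:
1. Fix two or three balancing factors, such as baseline prescription rate, number of high-risk attenders and deprivation index, and extract them for each centre.
2. List the 126 possible 5:4 splits and keep about the best-balanced half (63).
3. Check that no pair of centres is always or never together among those kept.
4. Have the staff outside the project draw one of them at random.
5. Include the baseline rate in the analysis model where the outcome has one.

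If the full protocol already contains such a procedure, stating it in the article is enough.

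The cost is a short program and a record extraction brought forward. Allocation has to wait until every centre has joined, and any permutation test must use only the retained splits. Keeping 32 would balance more tightly but leaves only one split that can reach the 5% level, so about half is the better compromise here.
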